**Methods/design:**

This paper focuses on the design of a health-economic, prospective, randomized, double-blind, multicenter study with three parallel arms carried out in France. This study assesses the cost-effectiveness of the adjunctive and maintenance low frequency rTMS on the right dorsolateral prefrontal cortex versus TAU alone. A total of 318 patients suffering from a current TRD will be enrolled. The primary endpoint is to investigate the incremental cost-effectiveness ratio (ICER) (ratio costs / quality-adjusted life-years [QALY] measured by the Euroqol Five Dimension Questionnaire) over 12 months in a population of patients assigned to one of three arms: systematic M-rTMS for responders (arm A); additional new rTMS cure in case of mood deterioration among responders (arm B); and a placebo arm (arm C) in which responders are allocated in two subgroups: sham systematic M-rTMS and supplementary rTMS course in case of mood deterioration. ICER and QALYs will be compared between arm A or B versus arm C. The secondary endpoints in each three arms will be: ICER at 24 months; the cost-utility ratio analysis at 12 and 24 months; 5-year budget impact analysis; and prognosis factors of rTMS. The following criteria will be compared between arm A or B and arm C: rates of responders; remission and disease-free survival; clinical evolution; tolerance; observance; treatment modifications; hospitalization; suicide attempts; work stoppage; marital / professional statues; and quality of life at 12 and 24 months.

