However, the rates of relapse and recurrence at 6-month follow-up may be comparable to the ECT [27]. These rates are in the range of 60% without consolidation to 30% with consolidation (pharmacological therapies or consolidation ECT) [28]. Having these comments, two therapeutic strategies are possible: a further rTMS cure can be performed at the first sign of relapse or recurrence [29], especially for patients with a good previous response [30]; or systematic maintenance rTMS (M-rTMS) can be carried out in the immediate future [31]. It is, therefore, essential to evaluate the cost-effectiveness of these alternatives treatment for TRD. It is already established that rTMS is more cost-effective (efficiency) than placebo [32] and rTMS is more efficient than a third-line antidepressant treatment in an Australian context [33]. But no controlled study compared in the long term (12 months) the cost-effectiveness of these two rTMS therapeutic strategies versus treatment as usual (TAU) alone (any therapeutic strategy agreed to by patients and psychiatrists including medication, ECT, and psychotherapy). Our main hypothesis is that additional M-rTMS will be more cost-effective at 1 year than TAU alone.

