### Secondary outcome measures

The secondary endpoints in each of the three arms are: ICER at 24 months after the last rTMS or placebo session; the cost–utility ratio analysis over 12 and 24 months; 5-year budget impact analysis of the most efficient therapeutic strategies; and prognosis factors of maintenance after a response to an initial rTMS cure. Moreover, the following criteria will be compared between arms A and C, and between arms B and C: rates of responders; remission; disease-free survival at 12 and 24 months; depressive symptomatology evolution; tolerance; observance; treatment modifications; number of suicide attempts and suicide achieved; marital / professional status; and quality of life at 12 and 24 months.

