### Statistical analysis

Descriptive analysis of the data collected during each patient evaluation will be carried up until the final evaluation. Specific time points for analysis in the three groups are: baseline; at 1 month after the last rTMS or sham sessions; and 12 and 24 months after the end of the first rTMS or sham course. Continuous variables will be described using median, standard deviation, minimal, maximal, and range for quantitative variables; qualitative variables will be described using frequencies and percentages. No data about quality of life, healthcare consumed, and the cost are available in the literature for this indication, making a priori the calculation of number of individuals needed impossible. The number of participants required for the present study was calculated according to the expected and sustained response in each arm (> 50% decrease in MADRS total score). This rate of responder after the rTMS cure is estimated at 60% in arms A and B at 1 year with 50% of success of rTMS [23, 48]. According to the literature, we hypothesized a rate of 30% maintained response at 1 year for arm A [23, 31, 49, 50] and arm B [23, 50–52], and 11% for arm C [53]. Assuming a 5% (bilateral) type I error, a power of 80%, and an attrition rate of 80%, a total of 318 individuals is required (106 in each arm). The study includes three arms, but only two comparisons will be carried out: arm A versus arm C, and arm B versus arm C.

For the ICER, resources consumed, including costs and QALY, will be presented with average and dispersion for each group. The comparison between cost, QALY, and the years of life gained in each arm, including ICER analysis, will be evaluated with the estimation of their standard deviation and their corresponding 95% confidence intervals (CI) following the non-parametric bootstrap method [54]. Tables will present differences between the three groups including their costs, QALY, and ICER. The ICER is calculated to consider the possibilities of vast dominance between these strategies [55]. For example, the ICER between arms A and C will be calculated as follows:

$$ ICER=\frac{C_{armA}-{C}_{armC}}{QALYs_{armA}-{QALYs}_{armC}} $$

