*C*_*armA*_ and *C*_*armC*_ correspond to the costs of depression in each arm and are the QALYs’ gain associated with the rTMS maintenance versus usual cares without rTMS (placebo). At the end, a univariate and determinate sensibility analysis will be estimate with the Tornado method to evaluate the robustness of the resultants concerning the variation in the cost of rTMS sessions and the hypothesis of their pricing.

To estimate the costs of depression, clinical data matching the eCRF and the NHSD will be applied using the patient identification number. If there is a baseline deviation between arms of the study about the quality of life estimated with the EQ-5D, two analyses will be conducted: one with the quality of life raw score; and another with adjusted scores using a logistic regression model [56]. The cost–utility and EQ-5D analysis will be conducted according to the intent-to-treat (ITT) principle on two samples: one sample with completed cases including participants with completed data; and another with an imputed sample in which missing data about cost and quality of life will be imputed according a multiple imputation method.

The rate of remission with their corresponding 95% CIs at 12 and 24 months will be compared between arm A versus arm C, and arm B versus arm C according to the generalized linear model (logistic model) to consider the repeated measurements as a random factor (stratification factor of the randomization). Plots of relapse-free survival at 12 and 24 months will be estimated according to the Kaplan–Meier method; they will be compared between arms A and B, and between arms B and C using the Log-Rank stratified test in each center. A Cox multivariate analysis will be applied to evaluate the sustainability of the response in the time.

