MADRS, MARS, CRS, and CGI scores with their corresponding 95% CIs will be compared between arms A and B, and between arms B and C according to a mixed logistic regression model to consider the center and repeated data as random factors. Modifications and side effects of pharmacological treatments will be described and compared using a Chi-squared test (or Fisher’s exact test, if appropriate). The number and percentage of suicidal attempts will be compared in the three arms using Fisher’s exact test. Marital status, professional status, and non-observance percentage (Maudsley Staging Model) will be described in the three arms at 12 and 24 months. The following criteria will be estimated for patients in each arm: responder and remission rate after rTMS or placebo cure; the number of cures prescribed; the duration of the rTMS cures and their side effects; observance rate; and the self-rated pain intensity of the procedure on a verbal analogue scale.

TMS indication is not yet approved in France. To evaluate its cost in the study in the French context, we used the cost-estimate of the rTMS cure calculated in France in 2015 [57]. According to this calculation, the hospital production cost of a rTMS session was estimated at 127.68 Euros (approximately US$141.64 calculated on Thursday, 22 August 2019, with 1 Euro = US$1.11) by session as detailed in Table 1.

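### For five secondary outcomes the analysis section compares A with B and B with C, contradicting the A–C and B–C contrasts set elsewhere in the protocol

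*Protocol article*

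**What the plan says.** Three places in the protocol article set the contrasts against arm C:

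- The abstract, under Methods/design: "The following criteria will be compared between arm A or B and arm C". The list that follows includes disease-free survival, clinical evolution and observance (adherence).
- Secondary outcome measures: "the following criteria will be compared between arms A and C, and between arms B and C". The list includes disease-free survival at 12 and 24 months, depressive symptoms over time and observance.
- Statistical analysis, at the end of the sample-size paragraph: "only two comparisons will be carried out: arm A versus arm C, and arm B versus arm C".

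Later in Statistical analysis, two sentences name a different pair of contrasts:

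- Relapse-free survival at 12 and 24 months: "they will be compared between arms A and B, and between arms B and C using the Log-Rank stratified test in each center".
- MADRS, MARS, CRS and CGI scores: these "will be compared between arms A and B, and between arms B and C according to a mixed logistic regression model".

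**The concern.** Neither of the last two sentences contains A–C, and both contain A–B. If they are followed as written, arm A (active cure plus systematic maintenance) has no specified comparison with the sham/TAU arm on relapse-free survival, depression severity, global severity or the two adherence scales. The endpoint section promises that comparison.

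Two things are at stake. First, an analyst who codes from the analysis text will run a different set of tests from one who codes from the endpoint section. Second, while both versions stand in print, either set can be defended after the results are known, so the contrast for these outcomes is not fixed in advance.

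**Working it through.** **Contrasts side by side**

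| Place in the protocol article | Outcome | Contrasts named |
|---|---|---|
| Abstract, Methods/design | Secondary criteria | A–C, B–C |
| Primary outcome measures; ICER text in Statistical analysis | ICER at 12 months | A–C, B–C (A–C formula written out) |
| Secondary outcome measures | Secondary criteria | A–C, B–C |
| Statistical analysis, sample-size paragraph | None specified | A–C, B–C only |
| Statistical analysis, logistic model | Remission at 12 and 24 months | A–C, B–C |
| Statistical analysis, log-rank test | Relapse-free survival | **A–B, B–C** |
| Statistical analysis, Cox model | Sustainability of response | None named |
| Statistical analysis, mixed model | MADRS, MARS, CRS, CGI | **A–B, B–C** |

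**Matching the outcomes.** I take relapse-free survival to be the endpoint listed as disease-free survival, since both are set at 12 and 24 months. MADRS is the measure of depressive symptoms. MARS and CRS are introduced under Assessments as the drug-compliance scales, so they correspond to observance. CGI is the loosest match; I place it under clinical evolution in the abstract. The count is 1 + 4 = 5 outcomes, in two sentences. In each sentence one contrast agrees with the endpoint section (B–C) and one does not (A–B in place of A–C).

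**Does anything else supply A–C?** The Cox sentence names no arms, so it does not close the gap. The remission sentence does use A–C, but for a different outcome. It comes immediately before the log-rank sentence, which shows the intended pattern.

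**Was A–B part of the sizing?** The inputs, from Statistical analysis, are sustained response at 1 year of 30% in A, 30% in B and 11% in C, 5% two-sided alpha, 80% power and 106 per arm. For two proportions with pooled variance under the null:

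n = [z(1−α/2)·√(2·p̄·(1−p̄)) + z(0.80)·√(p₁(1−p₁) + p₂(1−p₂))]² / (p₁−p₂)²

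Here p̄ = (0.30 + 0.11)/2 = 0.205, √(2 × 0.205 × 0.795) = 0.5709, √(0.21 + 0.0979) = 0.5549 and z(0.80) = 0.8416.

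- α = 0.05: (1.9600 × 0.5709 + 0.8416 × 0.5549)² / 0.19² = 69.7, so 70 per arm. With 20% attrition, 70/0.80 = 87.5, so 88. With the printed 80% attrition, 70/0.20 = 350. Neither is 106.
- α = 0.025: (2.2414 × 0.5709 + 0.8416 × 0.5549)² / 0.19² = 84.5, so 85 per arm. With 20% attrition, 84.5/0.80 = 105.6, so 106. Rounding to 85 first gives 85/0.80 = 106.25, so 107.

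The stated 106 is thus recovered if 5% is split over two comparisons and the printed 80% is read as retention. Both are my assumptions, because the article states neither. On that reading the size was built for exactly two comparisons, each 30% against 11%, that is A–C and B–C. Whatever the reading, A–B cannot have driven the size: the assumed difference is 30% − 30% = 0.

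The correction itself changes no figure.

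**The case against.** The best case on the other side has several parts.

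- **The plan does not drop A–C.** The abstract and Secondary outcome measures expressly promise it. This stands: the defect is a contradiction, and it would be wrong to say that the protocol has decided never to test A–C on these outcomes.
- **The main hypothesis is not touched.** A reader might infer that the primary test is damaged, because the Background states: "Our main hypothesis is that additional M-rTMS will be more cost-effective at 1 year than TAU alone". That hypothesis concerns cost-effectiveness, and its A–C contrast is intact in Primary outcome measures and in the ICER formula. This stands.
- **A–C is not a clean test of maintenance.** Arm A receives an active cure and arm C a sham cure, so A–C mixes the effect of the cure with that of maintenance. A–B shares the active cure and differs in strategy after response, so it is a meaningful question. This stands, but A–B is still not the contrast that the endpoint section promises.
- **Lack of power for A–B.** It is tempting to say that A–B would reject only at the alpha rate, since A and B are both assumed at 30%. That assumption covers sustained response at 1 year only. Arm B is re-treated at signs of relapse, so equal response at 1 year is compatible with different times to relapse, and the article assumes nothing about MADRS, MARS, CRS or CGI. None of the five outcomes was sized for any contrast.
- **The two-comparison sentence may be limited to the sized comparisons.** This is possible. The same section plans a three-arm Fisher test for suicide attempts and tables of differences between the three groups. Secondary outcome measures is therefore the firmer ground, and the contradiction holds without that sentence.
- **It is only a slip.** Plausible, given the remission sentence. But the same pair appears twice, for two different methods, so a reader cannot safely correct it unaided.

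**Conclusion.** The point holds as an internal contradiction. For relapse-free survival and the MADRS, MARS, CRS and CGI scores, the analysis text specifies A–B and B–C where the endpoint section and the abstract specify A–C and B–C. Followed literally, it omits one promised contrast on each of five secondary outcomes and adds one that was not part of the sample-size calculation. The primary ICER and the remission analysis are unaffected.

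The count of five assumes that relapse-free and disease-free survival are the same endpoint and that CGI belongs to clinical evolution. If CGI were left out, four outcomes would remain and the conclusion would be the same.

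Severity: should-fix, because the outcomes are secondary and the promised contrasts are stated elsewhere in the same document.

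**What to change.** In the log-rank sentence and in the sentence on the MADRS, MARS, CRS and CGI scores, name the pairs as A versus C and B versus C, to match Secondary outcome measures.

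If A–B is also wanted, add it explicitly as an additional comparison outside the two planned ones, and amend the sentence at the end of the sample-size paragraph so that it no longer excludes it.

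The cost is two wording corrections, plus one more if A–B is kept. No patients, visits or data are needed. The change should be made before unblinding, so that the contrasts are fixed without knowledge of the results.

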### Inclusion criteria

The 318 patients aged ≥18 years must present with a current depressive episode with duration between 12 weeks and 3 years considered major according the Diagnostic and Statistical Manual of Mental Disorders, 5th edition (DSM-5) [34], with a MADRS score of ≥ 20 [35] and treatment-resistant with an absence of remission after at least two different antidepressants lines at an effective dosage over a period of 6 weeks during the current episode. TRD includes resistance to antidepressants and validated potentialization agents as quetiapine or lithium [36]. The current treatment may have to be stable for 6 weeks before the baseline and to be continued at a stable dose throughout initial rTMS course. Each individual must be able to: understand the information; take a decision; volunteer to participate; complete the required questionnaire; take orally administrated treatment independently or have the adequate assistance to do so throughout the study; and go to the research center for successive follow-up visits.

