### Assessments

The following variables are documented during the baseline visit: sociodemographic (date of birth, age, gender, laterality, professional and marital status); medical history (length of illness, duration of the current episode, co-morbidities (psychiatric, addictive, somatic); and current treatment degree of prior therapeutic resistance according to the Maudsley Staging Model (MSM) [37]).

The following variables are regularly evaluated from the beginning to the end of the study, as shown in Table 1: intensity of the depression according to the MADRS [35]; the Beck Depression Inventory 13 items (BDI 13) [38]; the Clinical Global Impression - Severity (CGI-S) [39]; QALY evaluation by the Euroqol Five Dimensions Questionnaire (EQ-5D) [40]; the quality of life with the Short-Form 36 Health Survey (SF-36) [41]; the drug compliance according the Medication Adherence Rating Scale (MARS) [42] and the Compliance Rating Scale (CRS) [43, 44]; and pharmacological and non-pharmacological treatments statement with the eCRF. The response will be defined by a 50% reduction of MADRS, and remission by MADRS score of < 8. All significant side effects or adverse events will be reported in the eCRF by the research team.

**Table 1 Tab1:** Hospital production costs in France for a rTMS session

Medical	
Medical time	€39 (US$43.26)
Nurse time	€32 (US$35.50)
Equipment	€33.57 (US$37.24)
Structural expenses	€23.11 (US$25.64)
Total	€127.68 (US$141.64)

Potential explanatory variables to evaluate the depression economic cost are: formal and informal cares consumption (eCRF questionnaire); depression’s socio-professional aftermath with the Work Productivity and Activity Impairment (WPAI) [45] and eCRF questionnaire; health economic analysis with micro-costing; and data extracted from the National Health System Database of Health (NHSD) with the French hospital expenditure database (E.U. Program of Medicalization of Information Systems [PMSI]). Data from the NHSD include: medical consultations; hospitalizations; pharmacological treatments; work stoppages; daily allowances; care-related transports; imagery and biology; nursing cares; and losses of production in association with the WPAI.

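### MADRS, MARS, CRS and CGI scores are given a mixed logistic model with no cut-off or ordinal form, on contrasts that conflict with the rest of the plan, and non-observance is tied to the wrong scale

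*Protocol article*

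**What the plan says.** All references are to the protocol article.

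- **Model for the scores (Statistical analysis).** The outcomes are listed as "MADRS, MARS, CRS, and CGI scores with their corresponding 95% CIs". The contrasts given for them are A with B and B with C. The method is stated in these words: "according to a mixed logistic regression model to consider the center and repeated data as random factors". Neither a dichotomy nor a cumulative-logit form is mentioned.
- **Nature of MADRS.** Patients enter "with a MADRS score of ≥ 20" (Inclusion criteria). Assessments adds: "The response will be defined by a 50% reduction of MADRS, and remission by MADRS score of < 8".
- **Model for remission (Statistical analysis).** Remission at 12 and 24 months is compared separately, "according to the generalized linear model (logistic model) to consider the repeated measurements as a random factor".
- **Contrasts.** Secondary outcome measures compares arm A with arm C and arm B with arm C. Statistical analysis says these are the only two comparisons to be made.
- **Non-observance (Statistical analysis).** The article will describe the "non-observance percentage (Maudsley Staging Model") in each arm at 12 and 24 months. Assessments lists, among the baseline variables, "current treatment degree of prior therapeutic resistance according to the Maudsley Staging Model (MSM"). It assigns drug compliance to MARS and CRS, which belong to the set of instruments repeated from start to end of the study.

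**The concern.** The four outcomes are named as scores and are measured repeatedly. Logistic regression, without further qualification, models the probability of a binary event and returns odds ratios. An analyst who follows the sentence must first decide what the event is, or must decide that an ordinal model was meant. The article settles neither, so the choice could be made after data are available.

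The contrasts add to this. A–B and B–C leave out A–C for the scores, so systematic maintenance rTMS would not be compared with placebo on symptom severity or adherence. That is one of the two comparisons the trial is meant to make.

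The Maudsley label is a separate error of the same kind. A baseline staging of treatment resistance cannot yield a percentage of non-observance at 12 or 24 months.

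Symptom evolution and observance, both listed secondary endpoints, are at stake.

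**Working it through.** The article states no figure that depends on this sentence, so there is nothing to reproduce. The check is a comparison of sections, followed by one illustration.

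**Step 1. Could binary versions of the scores be meant?**

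| Score | Cut-off in the article | Separate comparison of the binary outcome |
|---|---|---|
| MADRS | Response: 50% reduction; remission: below 8 | Logistic model for remission. For response, post-cure rates are only estimated per arm |
| MARS | None | None |
| CRS | None | None |
| CGI | None | None |

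For three of the four scores this reading has nothing to work with. For MADRS it would repeat the remission analysis or supply a model for response. In either case the evolution of symptoms on the MADRS itself would have no analysis.

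**Step 2. Could an ordinal logistic model be meant?** It would need no cut-off, and it is a reasonable choice for CGI-S. The article does not say so. For a total with as many values as the MADRS it would be an unusual choice, and it would give odds ratios rather than differences in score points.

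**Step 3. Contrasts.** The score sentence has A–B and B–C. Secondary outcome measures and the sample-size paragraph of Statistical analysis both have A–C and B–C. Only B–C is common to both.

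**Step 4. Non-observance.** Set side by side, the label in Statistical analysis and the description in Assessments disagree on the construct (adherence against prior resistance) and on timing (12 and 24 months against baseline). MARS and CRS agree with the endpoint on the construct and are collected repeatedly.

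**Illustration only: what dichotomising could cost.** Assume a normally distributed score with one measurement per patient. The share of information kept after a cut at c standard deviations from the mean is φ(c)² / [p(1 − p)], with p = Φ(c):

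- c = 0 (50/50 split): 2/π = 0.637, a loss of about 36%
- c = 0.5 (69/31 split): 0.581
- c = 1.0 (84/16 split): 0.439

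For an assumed standardised difference of 0.4, two-sided 5% and 80% power:

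- Comparing means: 2 × (1.960 + 0.842)² / 0.4² = 98.1, so 99 per arm.
- After a median cut the proportions are Φ(0.2) = 0.579 and Φ(−0.2) = 0.421, which gives 155 per arm.

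The ratio 99/155 = 0.64 agrees with 2/π. Neither the 0.4 nor the median cut comes from the article.

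**The case against.** **Logistic models are not only for binary outcomes.** A proportional-odds mixed model is a logistic model, needs no cut-off, and suits ordered scores. This stands. A reader might infer that the analysis cannot be run, or that it forces a dichotomy. The article does not support that. It promises that scores will be compared with confidence intervals, without saying that the estimate is a mean difference. What remains is that the form is not stated and that the ordinary reading does not fit the outcome.

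**The article does give MADRS cut-offs.** This also stands. A reader might go on to infer that response and remission are both already analysed, so that a binary reading would be wholly redundant. Only remission has its own logistic comparison. Response rates are to be compared under Secondary outcome measures, yet Statistical analysis only estimates post-cure rates per arm, and the Cox model concerns how long response lasts. The mixed logistic model might therefore have been intended for MADRS response. That would not explain its use for MARS, CRS and CGI.

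**The word may be a slip for linear.** Possibly. The printed plan would then still name the wrong model. Logistic regression is also named for adjusting EQ-5D scores, so the wording is not isolated.

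**The efficiency loss is not a trial figure.** Agreed. A reader might turn the 36% into a loss of about 38 of 106 patients per arm (0.363 × 106). No section proposes a median split, the MADRS cut-offs are not medians, 106 is a count before attrition, and the data are repeated. If the model were ordinal, the usual large-sample efficiency for a normal score is about 3/π = 0.955, a loss of about 5%.

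**The Maudsley label costs little.** True. Non-observance is only described, with no test, and the MARS and CRS data will exist. A reader might infer that the endpoint is lost, but only its label is wrong.

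**Conclusion.** The point holds in a limited form. As written, the model named for the four scores does not suit them, and no cut-off or ordinal form is given that would make it suit. The contrasts in that sentence contradict two other places in the article. The instrument attached to non-observance is the wrong one by the article's own description.

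No stated figure changes. The efficiency figures are hypothetical: they assume a normal score, a single measurement and a chosen cut. The conclusion rests on the ordinary meaning of logistic regression and on the article's text alone. A statistical analysis plan that is not shown may already specify the model, but the published wording would still need correcting. Only secondary endpoints are touched. The primary ICER analysis and the sample size are not affected, so the correction should be made but is not critical.

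**What to change.** 1. **Model.** Replace the mixed logistic model by a linear mixed model for repeated measures for MADRS, MARS and CRS. For CGI-S, name either a linear or a proportional-odds mixed model. Include baseline score, centre and a patient random effect. Finer detail can sit in the statistical analysis plan.
2. **Contrasts.** Report A–C and B–C estimates with 95% confidence intervals at 12 and 24 months. State openly that these replace the A–B and B–C contrasts now printed for the scores, so that the sentence agrees with Secondary outcome measures and with the two comparisons fixed in Statistical analysis.
3. **Binary outcomes.** If the logistic model was intended for MADRS response, say so separately, using the definition in Assessments.
4. **Non-observance.** Replace the Maudsley Staging Model by MARS and CRS, and keep the Maudsley model as a baseline measure of resistance.

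The cost is a change of wording in the protocol or the statistical analysis plan. No visit, instrument or patient number changes, because the article already has these scales collected repeatedly. The changes should be dated before any comparison between arms is seen.

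### The stated suicide analysis omits completed suicides and uses a three-arm comparison, so it does not match the protocol's own endpoint or its two planned contrasts

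*Protocol article*

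**What the plan says.** Four places in the Protocol article bear on this.

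- **Secondary outcome measures** introduces a list with "the following criteria will be compared between arms A and C, and between arms B and C". One item on it is "number of suicide attempts and suicide achieved".
- **Abstract, Methods/design** gives the same pairing: "The following criteria will be compared between arm A or B and arm C". Its list names suicide attempts but not completed suicides.
- **Statistical analysis**, at the end of the sample-size paragraph, sets a rule for the whole study: "only two comparisons will be carried out: arm A versus arm C, and arm B versus arm C".
- **Statistical analysis**, further on, gives the only method for suicide: "The number and percentage of suicidal attempts will be compared in the three arms using" Fisher's exact test.

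No other sentence states how completed suicides will be analysed. Assessments adds a general recording rule: "All significant side effects or adverse events will be reported in the eCRF by the research team".

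**The concern.** The analysis sentence fixes an event, a set of arms and a test. Two of these three disagree with what the protocol sets elsewhere.

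- **Event.** The criterion covers attempts and completed suicides. The test covers attempts. A statistician who follows the sentence literally compares attempts and has no instruction for deaths by suicide.
- **Contrast.** The criterion is to be compared with sham separately for A and for B. The test is across three arms. A three-arm test addresses whether the arms differ in any way. It does not say whether either rTMS strategy differs from sham.

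A third matter is left open rather than contradicted. The sentence speaks of the number and percentage of attempts, so the unit could be patients or attempts. A patient can make several attempts in 24 months, and Fisher's exact test assumes independent units.

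At stake is whether the report can give a clear rTMS-versus-sham statement on suicide in a treatment-resistant population, with deaths included.

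**Working it through.** The protocol gives no attempt rate, effect or power for suicide, so there is no figure to reproduce. The main check is a comparison of the text.

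| Element | Criterion and comparison rule | Analysis sentence | Match? |
|---|---|---|---|
| Event | Attempts and completed suicides | Attempts only | No |
| Arms | A v C and B v C only | Three arms | No |
| Unit | Not stated | Not stated | Ambiguous |

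The two mismatches need no arithmetic. Two simulations show what the contrast and the unit could mean in practice. Both use 106 per arm (Statistical analysis) and p < 0.05, two-sided. **All event rates are assumptions.**

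**1. Three-arm test against the planned pairs.** Patients with an event are drawn as Binomial(106, p) in each arm. The three-arm test is the exact 3×2 Fisher test, and each pair uses the 2×2 Fisher test. There are 800 trials per row.

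| Assumed A / B / C | Three-arm rejects | A v C rejects | B v C rejects |
|---|---|---|---|
| 4% / 14% / 9% | 63.1% | 23.0% | 15.6% |
| 4% / 14% / 4% | 78.8% | 2.3% | 68.1% |
| 14% / 4% / 4% | 76.8% | 68.9% | 1.5% |
| 4% / 4% / 14% | 77.1% | 65.0% | 66.3% |

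The Monte Carlo standard error of the 63.1% is √(0.631 × 0.369 / 800) ≈ 1.7 points.

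In the first row the largest gap is A v B, 14 − 4 = 10 points, while each gap from sham is 5 points. The three-arm test picks up the A v B gap, which the plan does not set out to compare. In the other three rows it rejects about equally often (77–79%) whether B is the high arm, A is the high arm, or sham is the high arm. A rejection alone therefore does not show which planned contrast is responsible.

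**2. Unit of analysis, with no true difference.** Attempters per arm are drawn as Binomial(106, p) with the same p in both arms. Each attempter makes a geometric number of extra attempts with the mean shown. The 2×2 Fisher test is applied first to patients, then to attempts entered as if each were a patient. There are 20,000 trials per cell.

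| Assumed share attempting | Patients counted | Attempts, mean extra 0.5 | Mean extra 1 | Mean extra 2 |
|---|---|---|---|---|
| 5% | 2.1–2.3% | 12.2% | 22.1% | 36.9% |
| 10% | 2.9–3.0% | 14.4% | 25.2% | 41.9% |
| 15% | 2.9–3.3% | 16.2% | 28.4% | 46.4% |

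On patients the test is valid and conservative. With no repeat attempts the two counts coincide, and the error is 2–3%. The inflation appears only if attempts are the unit and some patients make more than one.

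**The case against.** The best reply is that this is condensed wording in a journal article. A number and percentage with Fisher's exact test is the ordinary way to report patients with an event, since a percentage needs a denominator and patients per arm is the natural one. The same section describes qualitative variables by frequencies and percentages. A phrase about three arms may be loose rather than a commitment to one overall test. Completed suicide is still a listed criterion, and significant adverse events go into the eCRF.

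Much of this stands, and it rules out several stronger readings that a reader might infer.

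- **That the plan counts attempts instead of patients.** The text allows that reading but does not establish it. The error rates of 12% and above in the working are conditional on it, and on assumed rates of repetition.
- **That completed suicides are dropped from the trial, or that an arm with more deaths would look safer.** They remain a criterion and would be recorded. The text also does not say whether a fatal attempt counts as an attempt. What is missing is their stated comparison.
- **That a three-arm Fisher test is invalid.** On patients it is valid. It answers a different question.
- **That suicide is the gravest risk the protocol names.** Study design, setting, and recruitment says no harm is anticipated. Suicide appears as a contributor to cost in the Background and as one of many secondary criteria.
- **That patients who stop attending contribute nothing, so linked data must be used.** No such rule is stated. Follow-up keeps non-responders in the study and adds telephone contacts at 15 and 21 months. The costing plan does use "data extracted from the National Health System Database of Health (NHSD) with the French hospital expenditure database", but the items listed there include no deaths, so adding it as a source for suicide events is an option and not the repair of an error.

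The reply does not remove the two mismatches. The article states an event and a set of arms for this analysis, and both differ from its own criterion and comparison rule. For remission, the same section names A v C and B v C explicitly, so it does name pairs where it means pairs. This is a contradiction between stated rules, not a detail left for the analysis plan.

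**Conclusion.** Wrong as written, of minor severity. That completed suicides lack a stated comparison, and that the three-arm comparison conflicts with the two planned contrasts, follows from the text alone. The ambiguous unit is a lesser point: it should be settled, but it is not shown to be an error.

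The size cannot be derived from the protocol, which gives no suicide rate. Under the assumed rates, a three-arm test can reject in about 63% of trials where the planned contrasts reject in 23% and 16%. If repeat attempts were entered separately, a nominal 5% test would run at about 12–16% with 0.5 extra attempts per attempter and 22–28% with one. These figures illustrate the mechanism and are not estimates for this trial.

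The point concerns one secondary criterion. It does not affect the primary ICER.

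**What to change.** Replace the suicide sentence in Statistical analysis with a rule that does the following:

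1. Defines the endpoint as patients with at least one suicide attempt or completed suicide, by 12 months and by 24 months.
2. Compares A v C and B v C, each by Fisher's exact test on patients, with a confidence interval for the difference in proportions.
3. Lists total attempts and completed suicides by arm, descriptively, so that repeat attempts and deaths stay visible separately.

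The cost is a few lines of wording. Attempts and completed suicides are already listed criteria, so no new variable is needed, and neither the sample size nor the primary analysis changes. One trade-off is that a combined endpoint mixes fatal and non-fatal events, which the separate listing in item 3 addresses.
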